### Descriptive statistics

For each group, we will determine descriptive statistics of the sample’s sociodemographic and clinical characteristics at baseline, and the outcome measures at all time points. Mean (standard deviation) and median values (interquartile range), or numbers and percentages will be reported. Univariate analysis of covariance will be used to investigate differences between the groups at baseline and the end of intervention.

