**Methods/Design:**

The study is a multicenter controlled trial. In total, 44 Norwegian municipalities will participate, including eight municipalities as a control group. For three municipalities with two zones, one will be assigned to the control group and the other to the intervention group. The experimental group will be offered reablement and the control group standard treatment. The sample will comprise approximately 750 participants. People will be eligible if they are home-dwelling adults, understand Norwegian, and have functional decline. Participants will be assessed at baseline, and after 10 weeks, 6 months, and 12 months. The primary outcome will be activity and participation measured by the Canadian Occupational Performance Measure. Physical functioning will be measured by the Short Physical Performance Battery and health-related quality of life by the European Quality of Life Scale. Coping will be measured by the Sense of Coherence questionnaire and mental health by the Mental Health Continuum Short Form. Costs will be generated based on registered working hours in different professions. Data analyses will be performed according to intention to treat. Univariate analysis of covariance will be used to investigate differences between the groups at baseline and the end of intervention. The data will be organized into two levels using a multilevel structure, i.e., individuals and municipalities, which will be analyzed using linear mixed-effects models. The working hours data (panel data) will be analyzed with random mixed-effects regression models. The cost-effectiveness of reablement will be evaluated according to the incremental cost-effectiveness ratio and uncertainty will be explored via the bootstrap method.

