### Sample size calculation

In an earlier study performed with older adults, the standard deviation for the primary outcome was shown to be 1.4 for COPM performance and 1.6 for COPM satisfaction [33]. The current trial is a multicenter study with 44 participating municipalities, so we expect that the variation in the COPM scores will be larger, and thus we employ a conservative estimate of 2.5 for the standard deviation. Furthermore, the allocation of participants to the intervention group or control group will not be randomized, and the number of participants in the intervention group will probably be three to four times that in the control group. We aim to detect a change of one point as statistically significant at a two-sided 5 % level and with a power of 80 %. Based on these estimates, sample size calculations indicate that we need to include 70 participants in the control group and 260 in the intervention group. Therefore, to consider the possibility of a relatively high dropout rate (up to 35 %) due to frail participants, a minimum of 107 and 400 participants will be included in the control and intervention groups, respectively.

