### Participants

The analysis will include all participants who answer the questionnaire both at baseline and follow-up, even if they drop out of the intervention (intention-to-treat analysis). *P*-values will be two-sided and significant at *P* ≤ 0.05.

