### Analysis of effectiveness

To evaluate whether the effect of the intervention varies according to the type of health problem(s), sociodemographic characteristics and home municipality will be used in linear mixed-effects models. Given the multilevel structure of the data (individuals over time within municipalities), we will control for stable differences between municipalities using a so-called fixed-effects model. Hence, we will control for time-invariant independent variables at the municipality level, such as the size of the municipality, demographics, and resources. In addition, the effect sizes will be calculated by dividing the difference of the mean change in the intervention groups and control groups by the standard deviation of the pretreatment scores.

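### The only test expressly tied to the end-of-intervention group difference is an ANCOVA with no stated municipality term, and the protocol does not say whether it or the mixed model governs

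*Protocol article*

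**What the plan says.** Two methods are named, in different places.

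- **ANCOVA.** Descriptive statistics states: "Univariate analysis of covariance will be used to investigate differences between the groups at baseline and the end of intervention". The abstract lists the same analysis among the main methods. Neither place names a municipality term or any covariate. The Participants paragraph of the analysis section sets the significance rule: P-"values will be two-sided and significant at" P ≤ 0.05.
- **Mixed models.** The abstract says "The data will be organized into two levels using a multilevel structure, i.e., individuals and municipalities", to be analysed with linear mixed-effects models. Statistical analysis describes individuals as nested within municipalities and treats municipalities as fixed effects. Analysis of effectiveness opens with the purpose: "To evaluate whether the effect of the intervention varies according to the type of health problem(s"). It then says that a fixed-effects model will control for stable differences between municipalities.

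Design and setting gives the allocation. There are 44 municipalities, eight of which act as controls. In three municipalities with two zones, one zone goes to each arm. Allocation is not randomised. No ICC or design effect is stated anywhere.

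**The concern.** Participants in one municipality share services, staff and local practice. The protocol itself expects standard care (control intervention section) and reablement (Discussion) to vary between municipalities. Because arm is set at municipality or zone level, this between-unit variation goes straight into the arm comparison. An individual-level ANCOVA treats every participant as independent, so its standard error is too small.

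The planned mixed models do not clearly remove the problem. Their stated purpose is effect variation, and no sentence makes their arm contrast the primary result. At a single time point, municipality fixed effects are confounded with arm everywhere except in the three split municipalities, so the 10-week contrast would rest on those three alone. In a model of change over time, fixed municipality intercepts remove stable differences but not municipality-level variation in change.

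At stake are the end-of-intervention p-value and confidence interval, and the lack of a rule if the two analyses disagree.

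**Working it through.** **The plan's own figure.** From Sample size calculation: "We aim to detect a change of one point as statistically significant at a two-sided" 5% level "with a power of 80"%, and "we employ a conservative estimate of 2.5 for the standard deviation". On the ratio, "the number of participants in the intervention group will probably be three to four times that in the control group".

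With a 1-point difference, SD 2.5 and a ratio of 260/70 = 3.71, the usual two-mean formula needs 63 and 234. The stated 70 and 260 is larger and gives about 84% power, so it errs on the safe side. For dropout, 70/0.65 = 107.7 and 260/0.65 = 400, against the stated 107 and 400. None of these figures includes an explicit design effect.

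**Number of allocation units.** The text does not say whether the eight control municipalities include the three split ones.

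- If they do: 5 + 3 = 8 control units and 36 + 3 = 39 intervention units.
- If they do not: 8 + 3 = 11 control units and 33 + 3 = 36 intervention units.

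Both readings give 47 units and both are carried through.

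**Formulas.** Let n_c and n_i be the numbers analysed, k_c and k_i the units, m = n/k, and ρ the ICC of the outcome after covariate adjustment (an assumption).

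- V = [1 + (m_c − 1)ρ]/n_c + [1 + (m_i − 1)ρ]/n_i − 2ρ × 3/(k_c k_i). The last term credits the three split municipalities.
- Design effect DE = V / (1/n_c + 1/n_i)
- Actual type I error = 2 × [1 − Φ(1.96/√DE)]

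**Worked case:** 107/400, 8/39 units, ρ = 0.05.

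- m_c = 13.375 and m_i = 10.256
- V = 1.6188/107 + 1.4628/400 − 0.3/312 = 0.01513 + 0.00366 − 0.00096 = 0.01782
- 1/107 + 1/400 = 0.01185, so DE = 1.50
- 1.96/√1.50 = 1.60, so type I error = 0.110

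**Type I error at nominal 0.05, equal cluster sizes** (each range covers 8/39 and 11/36 units; 750 is split 159/591 at 3.71:1):

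| Analysed | ICC 0.01 | 0.02 | 0.05 | 0.10 |
|---|---|---|---|---|
| 70/260 | 0.055–0.057 | 0.061–0.065 | 0.078–0.087 | 0.106–0.124 |
| 107/400 | 0.059–0.062 | 0.068–0.074 | 0.096–0.110 | 0.141–0.167 |
| 159/591 | 0.064–0.068 | 0.078–0.087 | 0.121–0.141 | 0.186–0.219 |

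Over this table DE runs from 1.05 to 2.55. Naive intervals are therefore too narrow by 1 − 1/√DE, about 2% to 37%.

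**Check by simulation.** An ANCOVA with a baseline covariate was simulated with unequal clusters (assumed coefficient of variation of cluster size 0.6) and 4,000 runs per cell. With ICC zero the rejection rate was 0.047–0.058, as it should be.

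| Analysed | ICC 0.01 | 0.02 | 0.05 | 0.10 |
|---|---|---|---|---|
| 70/260 | 0.055–0.060 | 0.067–0.074 | 0.090–0.110 | 0.130–0.161 |
| 107/400 | 0.063 | 0.079–0.084 | 0.128–0.140 | 0.186–0.206 |
| 159/591 | 0.068–0.073 | 0.092–0.107 | 0.158–0.184 | 0.236–0.284 |

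**Power of a valid test.** With 70/260 and no clustering, the standardised effect is 1/[2.5 × √(1/70 + 1/260)] = 2.97, which gives 84% power. Dividing by √DE for 8/39 units (DE = 1.12, 1.31, 1.62) gives about 80%, 74% and 65% at ICC 0.02, 0.05 and 0.10. This is a normal approximation; small-sample degrees of freedom would lower these figures somewhat further.

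**The case against.** The best defence is that the protocol knows its data are clustered. The ANCOVA sentence sits under a heading on description. The section headed Analysis of effectiveness names mixed models and control for municipality, and the abstract does not limit those models to effect variation. A reader might therefore go too far in inferring that the protocol ignores clustering or names no other between-group analysis. It does neither, and that stronger reading fails. What remains is that the abstract presents the ANCOVA as a main method, that it is the one analysis tied by name to the end of intervention, and that no precedence is given.

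It can also be said that ANCOVA terms are commonly left to an analysis plan. That is fair for covariates. Here, though, a stated method conflicts with the stated allocation and nesting, and leaving its terms unlisted does not resolve which analysis governs.

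Two further inferences should not be drawn. A baseline ANCOVA is not impossible for lack of an earlier score, because age, gender, education and other variables could be covariates. The abstract's two levels, set against individuals over time within municipalities in the main text, look like condensation and not a consequential contradiction.

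Finally, municipality fixed effects are a deliberate choice in a non-randomised study, and the Discussion uses baseline comparability when interpreting results. Both points stand, so neither feature needs to be removed.

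**Conclusion.** The point holds in this form: the test expressly assigned to the end-of-intervention difference has no stated allowance for clustering, and the protocol does not say which analysis carries the primary inference. The direction is certain for any positive ICC; the size is conditional.

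A reader might infer that false positives are two to four times the nominal rate. The documents do not support that as a general statement, because they give no ICC. With equal clusters, that range needs an assumed ICC of about 0.05 to 0.10 with roughly 490 to 750 analysed. At ICC 0.01 to 0.02 the inflation is modest, about 1.1 to 1.7 times (0.055 to 0.087). A doubling with 70/260 analysed needs an ICC of about 0.07 to 0.09. The highest simulated value, 0.284, needs ICC 0.10, all 750 analysed and unequal clusters together.

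**What to change.** Change the analysis wording in three places.

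1. In Descriptive statistics and the abstract, say that the ANCOVA is descriptive, or give it cluster-adjusted standard errors and degrees of freedom.
2. In Analysis of effectiveness, name the governing test: the baseline-adjusted 10-week arm contrast from a model that accounts for clustering by allocation unit (municipality or zone). One example is a random allocation-unit effect with a small-sample degrees-of-freedom correction, needed because there are only 8 to 11 control units.
3. Keep the municipality fixed-effects model of change over time as a supporting analysis, since it removes stable municipality differences that a random effect does not fully remove. State that it does not override the governing test.

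Baseline comparisons can stay.

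No new data are needed. The cost is wider, correct confidence intervals and some loss of power: with 70/260 analysed, from 84% to about 74% at an assumed ICC of 0.05. Recruiting toward the planned 750 would offset part of this.

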### Interventions

#### Reablement

Reablement is an intensive, interdisciplinary intervention. In general, the intervention lasts for a period of 3–10 weeks. To enable and enhance activity performance, it is crucial to acknowledge that the person is the expert on her/his own life. The main focus is to establish a dialog to identify activities that the individual perceives as meaningful to work on or to improve. The intervention is targeted to achieving these activity goals. Therefore, the patient-specific Canadian Occupational Performance Measure (COPM) will be used as part of the baseline assessments to give directions for the modeling of the reablement intervention. The COPM interview and scoring start with the following question: “What are the most important activities in your life now?” During the COPM assessment, the participant will define up to five activity goals that are essential to her or him. Based on these goals, a rehabilitation plan will be developed to promote a match between the activities and goals identified by participants, and professional initiatives. Intensive attention will be given to encourage participation and stimulate daily training for the participants, including performing their daily tasks. Individual tailoring is a major principle of reablement, so the content of the intervention will vary among participants, although the basic features are the same. Table 1 gives an overview of the content of the intervention, including fundamental principles and key components.

**Table 1 Tab1:** Content of the reablement intervention

Fundamental principles	Process, key components
• The rehabilitation period will be a maximum of 10 weeks.	• *Training in daily activities* such as personal hygiene, climbing stairs, family visits, cleaning the house, being able to write, or walking indoors/outdoors.
• A person-centered, resource-oriented, and interdisciplinary approach will be applied.	

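### The end-of-intervention ANCOVA pools one residual variance by default at about 3.7 intervention participants per control, so its standard error is vulnerable if the arms differ in spread

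*Protocol article*

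**What the plan says.** Under Descriptive statistics the Protocol article states: "Univariate analysis of covariance will be used to investigate differences between the groups at baseline and the end of intervention". The abstract repeats this among the analysis methods. Neither place says how the residual variance is modelled or which standard errors are used.

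Under Sample size calculation, allocation is described as not randomised and "the number of participants in the intervention group will probably be three to four times that in the control group". One SD serves both arms: "we employ a conservative estimate of 2.5 for the standard deviation". The 1.4 and 1.6 cited from an earlier study belong to the two COPM scales, not to two arms. The target is one COPM point, "statistically significant at a two-sided 5 % level and with a power of 80"%. This leads to 70 controls and 260 intervention participants, or 107 and 400 after allowing for up to 35% dropout.

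On content, the Reablement section says that "the content of the intervention will vary among participants, although the basic features are the same". The section on the control intervention likewise says that standard care differs between participants and between municipalities.

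Analysis of effectiveness specifies linear mixed-effects models with fixed effects for municipality. It introduces them chiefly to examine whether the effect differs by health problem, sociodemographic characteristics and municipality.

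**The concern.** A pooled residual variance is weighted by arm size, so at 70 against 260 it is close to the variance of the intervention arm. Most of the sampling error of the group difference, however, comes from the small control arm. If the arms differ in residual spread, the standard error is then too small or too large, depending on which arm is the more variable. With equal arm sizes the two effects cancel.

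Randomisation would give some protection: if treatment affected nobody, both arms would have the same outcome distribution. Here municipalities and zones were allocated on practical grounds, so residual spread may differ even with no treatment effect. The sponsor itself argues that adding municipalities increases COPM variation, and the two arms draw on very different numbers of municipalities.

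At stake is the interval for the COPM difference at the end of intervention. If controls are more variable, the test rejects too often. If intervention participants are, it rejects too rarely and loses power. The direction is unknown in advance, so either result could be challenged.

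**Working it through.** **Inputs from the Protocol article (Sample size calculation):** n₀ = 70 controls, n₁ = 260 intervention participants, SD 2.5, difference 1 point, two-sided 5%, power 80%, dropout 35%.

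**Assumed, because the article gives no value:** the ratio of residual SDs between arms, shown at 1.1, 1.25 and 1.5 in each direction. Participants are treated as independent.

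**1. The plan's own figure.** The ratio is 260/70 = 3.71. The normal formula gives

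n₀ = (1.96 + 0.8416)² × 2.5² × (1 + 70/260) = 62.3, so 63 controls and 234 intervention participants.

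The stated 70 and 260 exceed this. With them the standard error is 2.5 × √(1/70 + 1/260) = 0.337, and power is Φ(1/0.337 − 1.96) ≈ 84%. For dropout, 70/0.65 = 107.7 and 260/0.65 = 400. The planned numbers are slightly conservative and raise no difficulty here.

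**2. Calibration of the pooled test.** Let s₀ and s₁ be the residual SDs of the control and intervention arms. Then

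- s_p² = [(n₀ − 1)s₀² + (n₁ − 1)s₁²] / (n₀ + n₁ − 2)
- R² = s_p²(1/n₀ + 1/n₁) / (s₀²/n₀ + s₁²/n₁)
- type I error ≈ 2[1 − Φ(1.96 R)]

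R is the model standard error divided by the true one.

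*Controls more variable, s₀ = 1.5, s₁ = 1:* s_p² = (69 × 2.25 + 259)/328 = 1.263. R² = 1.263 × 0.01813 / 0.03599 = 0.636, so R = 0.80. Type I error = 2[1 − Φ(1.563)] = 11.8%.

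*Intervention more variable, s₀ = 1, s₁ = 1.5:* s_p² = (69 + 259 × 2.25)/328 = 1.987. R² = 1.987 × 0.01813 / 0.02294 = 1.571, so R = 1.25. Type I error = 2[1 − Φ(2.456)] = 1.4%.

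| Assumed SD ratio | Controls more variable: R, type I error | Intervention more variable: R, type I error |
|---|---|---|
| 1.1 | 0.95, 6.4% | 1.06, 3.8% |
| 1.25 | 0.88, 8.4% | 1.14, 2.6% |
| 1.5 | 0.80, 11.8% | 1.25, 1.4% |

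At a ratio of 1.5, allocation of 3:1 gives 10.7% and 1.7%, and 4:1 gives about 12.2% and 1.3%. With 165 per arm the error stays at 5.0%.

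**3. Simulation.** ANCOVA with a baseline covariate and arm-specific residual SDs, 40,000 runs per setting, ratio 1.5: 11.9% and 1.4% at 70/260; 11.5% and 1.4% at 107/400. With HC3 standard errors the rates were 4.7% to 5.1%.

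**4. Why HC3 alone is not the answer.** Step 3 assumes independence, whereas participants are nested in municipalities. As an illustration, 44 municipalities with three split into two zones make 47 units, about 330/47 = 7.0 participants each. At an assumed residual ICC of 0.05 the design effect is 1 + 6.0 × 0.05 = 1.30. A 5% test that ignores it rejects with probability 2[1 − Φ(1.96/√1.30)], about 8 to 9%. HC3 does not correct this.

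**The case against.** The strongest reply is that the article never states a common variance. It names ANCOVA, and the form of the standard error is normally left to a statistical analysis plan, which is not shown and may already specify robust errors. That stands, and it rules out calling this an error or an omission. What remains is that unqualified ANCOVA conventionally means one residual variance, and that the article fixes the allocation which makes this matter.

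Second, a reader might infer from the tailored intervention and the mixed content of standard care that unequal spread is to be expected, or that 12% is this trial's error rate. The article supports neither. It describes content as varying in both arms, which indicates no direction and no size. Varied care is also not the same as different residual COPM variance after baseline adjustment, which is the quantity that counts. The 1.5 ratio is purely an assumption; at 1.1 the distortion is small.

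Third, the ANCOVA sentence stands under Descriptive statistics, while Analysis of effectiveness uses other models. The heading does not remove the point, because ANCOVA is the method explicitly named for the group difference at the end of intervention. But the percentages above were not derived for the mixed-effects models and should not be quoted for them.

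Fourth, the article already plans means and SDs by group at every time point, so unequal spread would be seen. That stands; reporting SDs by arm need not be requested. Seeing it after the event, however, leaves the choice of standard error to be made with the results in view.

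**Conclusion.** The point holds as a conditional vulnerability. At about 3.7:1 without randomisation, an ordinary ANCOVA has a miscalibrated standard error if residual SDs differ by arm, and the article gives no ground for assuming that they do not. For assumed ratios of 1.1 to 1.5 the type I error runs from about 6% to 12% in one direction and from about 4% to 1.4% in the other. These figures rest on 70 and 260 evaluable, independent participants and on SD ratios that the article does not supply. They show neither that the trial's error rate is wrong nor which way it would err. The case for acting is that protection is nearly free and is best fixed before the results are known.

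**What to change.** State in the analysis plan that the between-group COPM comparison at the end of intervention will use one of the following:

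- a mixed model that keeps the municipality level and has arm-specific residual variances; or
- standard errors robust to both unequal variance and clustering by municipality, with a small-sample correction.

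HC3 on its own is not sufficient, because it ignores the clustering.

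**Cost:** a sentence in the plan and slightly wider intervals if the variances prove equal. For the unadjusted comparison at 70/260 with equal variances, the separate-variance (Welch) degrees of freedom fall from 328 to about 109. The critical value then rises from 1.967 to 1.982, under 1%. Allowing for clustering may widen the interval further, but that reflects the nesting of participants in municipalities, not the allowance for unequal variance.
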